## Background

The increase in overweight and obesity rates is a major public health concern. In most countries it has affected all population groups regardless of sex, age, race, income or education level, but to varying extents [1]. Based on comparative studies with other European countries, Spain is at the forefront [1], one in four people is overweight or obese, ie 12.5 million people [2]. In fact, two out of three men are overweight and one of every six is obese, with a clear trend to increase in the forthcoming years [3].

Today it is accepted that obesity has a multifactorial origin [4,5] and is a known risk factor for numerous health problems, including high cholesterol, diabetes, hypertension, respiratory problems, musculoskeletal diseases, cardiovascular diseases, and some forms of cancer. Mortality also increases sharply once the overweight threshold is crossed [6,7].

Research has been very active in the last years trying to identify the most effective treatment for adult overweight and obesity [8-40]. A combination of caloric restriction with an increase in energy output by means of exercise has been proven in the hospital setting [41]. Results have been quite conclusive regarding aerobic exercise [9] and very restrictive caloric intake (less than 50% of kcal intake) [35]. But data are still scarce regarding the effect of a combination of strength and aerobic training and a much lesser restrictive hypocaloric diet on weight loss [35]. The PRONAF study wants to get deeper into the latter, also considering the Consensus Paper 2011 from the Spanish Society of Obesity Research (SEEDO), that has stated that the primary goal of treatment should not focus on achieving the ideal body weight, but to have smaller weight losses maintained in the long term [42].

Therefore, the main aim of the PRONAF study was to discover which is the most effective training protocol in combination with caloric restriction for overweight and obese subjects included in a specific intervention program. The aim of this paper is to describe the design and the evaluation methods used for the PRONAF study.

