### Population and sample size estimation

The estimation of the sample size was calculated to detect a main effect of the treatment on the percentage of body fat with a 80% statistical power at 5% significance, assuming a 0.80 correlation between repeated measures [43]. The initial calculated sample size per intervention group (n = 22) permits the detection of a large effect size (Cohen’s d = −0.8), as observed in a previous investigation [43].

The initial adjustment of sample size for dropouts carried out used a maximum of 25% of dropouts in each group [37]. Adjusted dropouts sample = n (1/1-R), where n = number of subjects not lost, and R = expected proportion for dropouts. With our data, the initial necessary sample size was: 88 (1 / 1–0.25) = 118 subjects or 29/30 in each intervention group, this being applicable for both the overweight and the obese interventions groups. A total of two hundred thirty nine people initiated the study, completing it 180 (75.3%), which supposed 59 dropouts for different reasons. For personal reasons 17 (28.8%), low exercise adherence 3 (5.1%), low diet adherence 6 (10.2%), job change 6 (10.2%), and lost interest 27 (45.8%).

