### Statistical analysis

The main independent variables of the study were: intervention group, age, gender, measurement (baseline – post) and BMI classification (overweight or obese). The delta percentage was calculated thought the standard formula: change (%) = [(post-test score − pre-test score)/pre-test score]*100. The power calculated previously to find significant differences between groups was 0.8 to fat mass (%).

Standard statistical methods will be used for the calculation of the means and standard deviation for all dependent variables. The statistical analysis will be as follows: 1) Univariate descriptive analysis, study of data distribution, basic statistics such as central and dispersion values. Pair comparison tests with previous analysis of the homogeneity of variance will be used. Pearson correlation coefficients, chi-squared tests and exact probability calculations will be also performed to study the relationship between quantitative and qualitative variables, respectively; 2) General lineal models, such a multivariate analysis (MANOVA) or two way analysis of variance (ANOVA) for repeated measures, will be used to determine differences among the four interventions groups and between baseline and post-training values. Compound symmetry, or sphericity, will be verified by the Mauchly test. When the assumption of sphericity would not be met, the significance of F ratios will be adjusted according to the Greenhouse-Geisser procedure. Multiple comparisons of ANOVAs will be made with the Bonferroni post -hoc test.

The analysis of the data will be done using statistical package SPSS (SPSS Inc., Chicago, Illinois, USA). The significant level will be set at α = 0.05.

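### The planned Bonferroni post-hoc test for the four-arm comparisons is valid, but Holm or Shaffer step-down adjustment is never less powerful at the same 5% familywise error

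*Protocol article*

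**What the plan says.** The Background section of the protocol article gives the purpose: "the main aim of the PRONAF study was to discover which is the most effective training protocol in combination with caloric restriction". The Statistical analysis section plans MANOVA or two-way repeated-measures ANOVA across the four intervention groups and the two measurement times, in SPSS. It then adds: "Multiple comparisons of ANOVAs will be made with the Bonferroni post -hoc test". The level is fixed in the same section: "The significant level will be set at α = 0.05".

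The section does not list which comparisons form the family. An unqualified Bonferroni post-hoc test across four groups is naturally read as all six pairs, each at 0.05/6.

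The sample size section names its target: "main effect of the treatment on the percentage of body fat with a 80% statistical power at 5% significance". The calculation takes the pre and post values to be correlated at 0.80. It concludes: "The initial calculated sample size per intervention group (n = 22) permits the detection of a large effect size", with Cohen's d of 0.8 in absolute value. After allowance for dropout the target is "118 subjects or 29/30 in each intervention group", applied to the overweight and the obese cohort alike.

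**The concern.** The main aim is to say which programme is the most effective. Under pairwise testing, that claim needs one arm to be shown better than each of the other three. Ordinary Bonferroni holds all six pairs to the strictest threshold, 0.0083, however many have already been rejected. Step-down procedures relax the threshold after each rejection without raising the familywise error, because fewer null hypotheses can still be true. A claim that needs three rejections together is where this relaxation helps. What is at stake is power on the main question, with the number of participants unchanged. The validity of the results is not at stake.

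**Working it through.** **Inputs.** From the protocol article: four arms per cohort, α = 0.05, n = 22 per arm, d = 0.8 in absolute value, correlation 0.80 between repeated measures. Assumed: two-sided tests, all six pairs in the family, equal n and equal variances, and d expressed on the raw cross-sectional SD, set to 1.

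**Step 1: reproduce n = 22.** The between-group main effect averages the pre and post values. Its SD is √((1 + 0.80)/2) = √0.90 = 0.949. Then

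n = 2 × [0.949 × (1.960 + 0.842)/0.8]² = 22.07 per group,

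and power at n = 22 is 79.9%. The planned figure is therefore recovered as a two-group main effect at an unadjusted 5%. The dropout step also reproduces: 88/(1 − 0.25) = 117.3, rounded up to 118.

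**Step 2: the other plausible scale.** In a pre-post repeated-measures ANOVA the group-by-time test is equivalent to a test on change scores. With d on the raw SD, the change-score SD is √(2 × (1 − 0.80)) = √0.40 = 0.632. The two SDs give the range.

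**Step 3: thresholds.** Pooled error df = 4 × 21 = 84. Order the six p-values from smallest to largest. Each is compared with 0.05 divided by:

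| Rank of p-value | Bonferroni | Holm | Shaffer (all pairs of four means) |
|---|---|---|---|
| 1 | 6 | 6 | 6 |
| 2 | 6 | 5 | 3 |
| 3 | 6 | 4 | 3 |
| 4 | 6 | 3 | 3 |
| 5 | 6 | 2 | 2 |
| 6 | 6 | 1 | 1 |

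Shaffer's divisors follow from logic: once one pair of four means differs, at most three of the equalities can still be true. The critical t values on 84 df are 2.70 for 0.05/6 and 2.44 for 0.05/3. No Holm or Shaffer divisor exceeds Bonferroni's, so every Bonferroni rejection is also a Holm and a Shaffer rejection. The first row is identical, so the chance of at least one rejection is the same for all three.

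**Step 4: simulation.** One arm is better by 0.8 than three equal arms, with 22 per arm and pooled-variance t tests.

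| SD | Quantity | Bonferroni | Holm | Shaffer |
|---|---|---|---|---|
| 0.949 | best arm beats all three | 29% | 35% | 40% |
| 0.949 | mean power per true pair | 54% | 57% | 61% |
| 0.949 | at least one rejection | 78% | 78% | 78% |
| 0.632 | best arm beats all three | 84% | 88% | 90% |
| 0.632 | mean power per true pair | 93% | 94–95% | 96% |
| 0.632 | at least one rejection | 99% | 99% | 99% |

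With no difference between arms, the familywise error is about 4% for all three.

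**Step 5: closely ranked arms.** If two arms lie midway between the best and the worst (means −0.8, −0.4, −0.4, 0), best-beats-all is 3.2%, 4.6% and 5.8% at SD 0.949, and 14.7%, 20.5% and 22.7% at SD 0.632, for Bonferroni, Holm and Shaffer in turn. The ordering holds, but none of the three separates such arms well.

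**The case against.** The strongest defence is that Bonferroni is a standard, valid procedure. It controls the familywise error, gives simple simultaneous intervals and contradicts nothing else in the article. That stands: the choice costs efficiency and is not an error. The gain is also modest on the change-score scale, where Bonferroni already reaches 84% and stepping down adds 4 to 6 points. That stands too, and is why the range is shown. A condensed article may leave the family of comparisons to a fuller plan. But the article does name the method, and the point concerns that named method, not missing detail.

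Two stronger readings are tempting, and neither is supported.

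- *Unadjusted arm tests.* The Statistical analysis section also says: "Pair comparison tests with previous analysis of the homogeneity of variance will be used". A reader might infer that the arms are compared there without correction. With six pairs and no true difference, that would give a false positive in about 20% of outcomes. The sentence belongs to the univariate descriptive step. It does not say that the tests compare arms or that they are unadjusted, while differences among the four groups are assigned to the ANOVA step with Bonferroni.
- *Multiple comparisons with the best.* Since the aim is to name the best arm, a reader might infer that Hsu's procedure should replace the pairwise tests. At 0.8 SD of the analysed outcome its best-beats-all probability is 49%, against 24% for Bonferroni. But the 49% uses a one-sided 5% critical value (2.09) against a two-sided one (2.70). At one-sided 2.5% (2.39) it is 36%, close to Shaffer's 34%. The procedure also says nothing about pairs that do not involve the best arm, and the plan sets out to test differences among all four.

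**Conclusion.** The point holds as a low-cost efficiency improvement. For hypothesis tests among the four arms, Bonferroni is uniformly dominated by Holm, and for all pairs by Shaffer, at the same strong 5% familywise error. With one arm better by d = 0.8 than three equal arms and 22 per arm, the chance of showing it better than all three others rises by about 6 points (Holm) or 10 to 11 points (Shaffer) at SD 0.949, and by about 4 or 6 points at SD 0.632. The first rejection is no easier to obtain.

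The dominance does not depend on any assumption about effect sizes. The size of the gain rests on two-sided tests, six pairs per cohort, equal n and variances, and d on the raw SD. Bonferroni remains valid, and results obtained with it would not be wrong.

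**What to change.** In the Statistical analysis section, replace the Bonferroni post-hoc test by Holm step-down adjustment of the pairwise p-values or, if all six pairs are compared, by Shaffer's. For estimation, keep simultaneous intervals by Bonferroni or Tukey-Kramer. Tukey-Kramer intervals are about 3% narrower here (critical value 2.62 against 2.70 on 84 df).

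The cost is a change of wording and the sorting and multiplying of six p-values per outcome. No further participants or measurements are needed. The downside is that the step-down tests have no simple matching simultaneous intervals. A pair may occasionally be significant by the test while its interval includes zero, so the plan should say that the step-down test decides and the interval describes.

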### Assessment for quality control

Previous to the start of the intervention we developed a protocol book with all the tests carried out in the pre and post intervention, plus the intervention procedures. An external observer followed the pilot study and his observations were included in the protocols. Weekly meetings during the pilot study were made with all the people involved in the project to train them and perform the protocol book.

At the end of the overweight intervention, the subjects filled in a satisfaction questionnaire. The results were included in the design of the obese intervention.

Finally, in order to clean the final data base of possible errors, a double data entry procedure was performed. Also an assessment of missing data and the identification of potential outliers were carried out.

## Discussion

The PRONAF study is the first randomized controlled intervention study performed in Spanish overweight and obese adults without any other associated disease with the aim of losing weight and improving several health-related parameters by means of combining caloric restriction and controlled training programs. One of the strengths of the PRONAF study is the multidisciplinary approach. A group of professionals and researchers with expertise in a specific field: physical activity and fitness, nutrition, body composition, genetics and biochemical markers have designed together the study protocols after an in-depth review of the state of the art in the literature [8-40]. Exercise protocols were tested in healthy subjects and study protocols harmonized in a pilot study [70,71].

The PRONAF study has both strengths and limitations. The main limitation is that the study did not include psychological control of the subjects. During the study and in the final questionnaire evaluation the subjects pointed out the need of some psychological support especially when the body weight changes were not so evident.

On the other hand, the PRONAF study has also several strengths: 1) the final sample size of our study was maintained according to the sample size estimation, keeping a low dropout rate similar to other studies [37,40,41]. It is important to note that there were no differences between groups in the number of dropouts. 2) During the training sessions the participants in the study were continuously monitored by certified trainers to ensure the correct execution of the exercises and the completion of each training session. 3) Inclusion of additional variables as visceral fat, blood lipid profile, and genotyping broadens the dimension of the PRONAF study.

In summary, feasibility of the PRONAF protocol has been proven. Transfer of knowledge is foreseen as a spin-off, in order that overweight and obese subjects can benefit from the results. The aim is to transfer it to sports centers. Effectiveness on individual health-related parameter will be analyzed in forthcoming publications.

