**Discussion:**

Feasibility of the study has been proven, with a low dropout rate which corresponds to the estimated sample size. Transfer of knowledge is foreseen as a spin-off, in order that overweight and obese subjects can benefit from the results. The aim is to transfer it to sports centres. Effectiveness on individual health-related parameter in order to determine the most effective training programme will be analysed in forthcoming publications.

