### Inclusion and exclusion criteria

Inclusion criteria included being male or female living in the Region of Madrid, being overweight (BMI 25–29.9 kg/m^2^) or obese (BMI: 30–34.9 kg/m^2^), middle-aged (from 18 to 50 years), having a sedentary lifestyles (< 30 min Physical Activity/day), being normoglycaemic, and non-smoker [37,41]. In the case of females, having regular menstrual cycles was required.

The exclusion criteria were suffering from a physical (orthopaedic limitations, stroke, etc.) and/or psychological (anorexia, bulimia, etc.) disease that may have precluded the performance of the requested strength or endurance training, intake of any medication (beta blockers, alcohol, etc.) known to influence physical performance or the interpretation of the results, having a history of systematic strength or endurance training (moderate to high intensity training more than once a week) in the year before the beginning of the study [37,40].

After the intervention period, participants who failed to comply with 90% assistance to the training sessions and less than 80% adherence to the diet were excluded from further analysis. The characteristics of the final sample (completers) are shown in Table 1.

**Table 1 T1:** Baseline data (n = 180)

	**Overweight n = 84**		**Obesity n = 96**	
	**Women**	**Men**	**Women**	**Men**
	**n = 48**	**n = 36**	**n = 48**	**n = 48**
Age (years)	37.29 ± 8.25	37.42 ± 8.02	39.02 ± 7.74	38.79 ± 7.99
Body Weight (kg)	73.5 ± 5.87	88.21 ± 8.13	88.33 ± 10.1	102.04 ± 8.94
Height (m)	1.62 ± 0.06	1.75 ± 0.07	1.64 ± 0.07	1.77 ± 0.06
BMI (kg/m^2^)	28.01 ± 1.32	28.57 ± 1.12	32.41 ± 1.85	32.4 ± 1.9
Body fat (%)	43.28 ± 3.62	33.8 ± 4.63	47.11 ± 3.49	38.17 ± 4.02
Body fat free mass (kg)	40.25 ± 4.3	55.99 ± 5.47	44.3 ± 4.71	58.63 ± 8.96
Bone mineral density (g/cm^2^)	1.18 ± 0.1	1.26 ± 0.09	1.21 ± 0.11	1.3 ± 0.1

Results are shown as Mean ± SD.

*Note*. BMI = Body Mass Index. Body fat, Body fat free mass and Bone mineral density calculated by Dual-energy x-ray absorptiometry (DXA).

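### The claim that the final sample and dropout matched the sample-size estimate is true only for the two cohorts pooled; the overweight cohort ended with 84 of 88 required completers and lost 29.4% against an allowance of 25%

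*Protocol article*

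**What the plan says.** The section on population and sample size estimation sizes the trial for body-fat percentage "with a 80% statistical power at 5% significance, assuming a 0.80 correlation between repeated measures". It gives 22 per intervention group, which "permits the detection of a large effect size" (Cohen's d of 0.8 in absolute value). For dropout it "used a maximum of 25% of dropouts in each group", which raises 88 to 118. It adds that this applies to the overweight and to the obese intervention groups. The Study design section fits that reading: the study was run twice, a year apart, with eight groups in all.

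The abstract reports 119 overweight and 120 obese participants randomised. Table 1, which describes the completers, is headed "Overweight n = 84" for the first cohort and gives 96 for the second. Overall dropout is stated only as a pooled figure: 59 of 239, or 24.7%.

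Two statements of attainment follow. The Discussion says that "the final sample size of our study was maintained according to the sample size estimation, keeping a low dropout rate similar to other studies". The abstract says that feasibility was shown, "with a low dropout rate which corresponds to the estimated sample size".

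**The concern.** The requirement was set for each cohort, but the statement that it was met is made for the whole study. When the article's own counts are split by cohort, the overweight intervention falls short on completers and exceeds the dropout allowance. The better retention in the obese intervention offsets this in the total.

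The claim is offered as evidence of feasibility and of an adequate sample, and the article says that results will follow in later publications. A later paper on the overweight cohort could cite this article for having reached its planned size, which it did not.

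**Working it through.** **Inputs**
- Required completers: 22 per arm, four arms, per cohort (Population and sample size estimation).
- Dropout allowance: at most 25% in each group (same section).
- Randomised: 119 overweight, 120 obese (abstract, Methods/design).
- Completers: 84 overweight, 96 obese (Table 1).
- Total dropouts: 59 of 239 (Population and sample size estimation).

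**The plan's own figure**
- 4 × 22 = 88 completers per cohort.
- 88 / (1 − 0.25) = 117.3, rounded up to 118. Per arm, 22 / 0.75 = 29.3, so 29 or 30. Both agree with the article.

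**Attainment by cohort**
- Overweight: 119 − 84 = 35 lost; 35/119 = 29.4%. Completers 84 against 88, 4 short (4/88 = 4.5%).
- Obese: 120 − 96 = 24 lost; 24/120 = 20.0%. Completers 96 against 88.
- Pooled: 35 + 24 = 59 lost, which matches the stated total; 59/239 = 24.7%. Completers 180 against 2 × 88 = 176.

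Because the two cohort losses add up to the stated 59, the counts are consistent with one another. Overweight enrolment (119) reached the planned 118, so the shortfall comes from attrition. A 25% loss from 119 would have left 0.75 × 119 = 89.25, about 89.

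**What follows for the arms**
- 84/4 = 21 on average, so at least one overweight arm has fewer than 22 completers.
- The cohort's 29.4% is a weighted average of the four arm rates, so at least one arm lost 29.4% or more, above the 25% allowance.

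**Cost in power**

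The article does not state the sidedness of the test or the scale of d. I assume a two-sided 5% level and a comparison of two arms. The reading closest to 22 per arm takes the between-group effect averaged over the two measurements, with SD factor √((1 + 0.80)/2) = 0.949. With the normal approximation, power = Φ(0.8/0.949 × √(n/2) − 1.96).
- n = 22: 79.9%.
- n = 21: 78.0%.

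The loss is about 2 points. Other readings of d give a different level of power but no larger loss:
- plain two-sample comparison, noncentral t: 73.6% at 22 and 71.6% at 21;
- change scores with d in raw SDs (SD factor √0.4), normal approximation: 98.7% and 98.4%.

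**The case against.** The strongest defence is that the Discussion sentence speaks of the study as a whole, and on that basis it is true: 180 exceeds 176 and 24.7% is below 25%. BMI class is listed among the independent variables, so a joint analysis is possible. The cohort counts are also not hidden, since anyone can combine the abstract with Table 1. This stands as far as it goes, and the pooled result should be kept in any correction. It does not rescue the blanket claim, because the sample-size section applies the requirement to each cohort.

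It is also fair to say that the 25% is a planning allowance used to inflate enrolment and that the article sets no feasibility threshold. Exceeding it in one cohort does not refute feasibility.

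Three stronger readings are tempting but not supported.
- A reader might compute two-sample power at 21 per arm, find 71.6% (43.7% with Bonferroni over six pairs), and blame the shortfall. The same test at the planned 22 gives 73.6% and 46.2%. Nearly all of the gap to 80% comes from the choice of test.
- A reader might infer that dropout truly differed between cohorts, or was concentrated in overweight women. The cohort difference is compatible with chance (Fisher p = 0.10), as is the variation over the four cohort-by-sex cells (chi-square p = 0.15). The document sets no target by sex.
- A reader might say that losses by arm go unreported. Figure 1, the participant flow diagram, is not visible in the text reviewed and may give them.

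**Conclusion.** The concern holds in a limited form. The attainment statements in the abstract and the Discussion are correct for the pooled sample and wrong for the overweight cohort, which missed both the completer target and the dropout allowance. That conclusion uses only counts printed in the article.

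The obese cohort met both figures in total; whether each of its arms did cannot be told from the text.

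The practical effect is small: 4 completers, and about 2 percentage points of power. The power figure assumes a two-sided test, the repeated-measures reading of d used above, and an even spread of the 84 over the arms. An uneven spread would change it for particular pairs of arms. This is a misstatement about sample size to be corrected in the wording; it does not show that the overweight comparison is seriously underpowered.

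**What to change.** In the abstract's Discussion paragraph and in the main Discussion, replace the general claim with the figures by cohort:
- overweight: 84 of 119 retained (29.4% lost), target of 88 and 25% planning allowance both missed;
- obese: 96 of 120 retained (20.0% lost), both met for the cohort in total;
- pooled: 180 of 239 retained (24.7% lost).

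Add one sentence saying that the planned 80% power is slightly reduced in the overweight comparison, by about 2 percentage points if the completers are evenly spread. Add losses by arm only if the participant flow diagram does not already show them.

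The cost is a few lines of text and a slightly less favourable statement of retention. No design element or analysis rule changes.
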